## Abstract

**Supplementary Information:**

The online version contains supplementary material available at 10.1007/s00787-024-02608-2.

## Background

According to the World Health Organization [1], 14% of adolescents worldwide experience a mental health disorder, but lifetime prevalence estimates have reached as high as 49.5% [2]. Research consistently shows that anxiety disorders (ADs) are the most common mental health conditions during adolescence [2–8], with the age of onset usually occurring in childhood or adolescence [9–11]. The presence of ADs during those periods has been linked to an increased likelihood of experiencing anxiety during emerging adulthood [12], and to a greater risk of presenting other disorders (e.g., substance and alcohol abuse/dependence, or major depressive disorder,[13]. Adolescent ADs have also been linked to significant short and long-term impairments across a broad spectrum of life domains [13–16]. Experiencing ADs during adolescence can hinder the acquisition of crucial competencies to adolescents overall development that can shape their future lives and lead to negative outcomes in adulthood [17]. Hence, increasing the understanding of the common mechanisms underlying mental health problems, with a particular focus on different ADs in adolescence, and how these mechanisms can be used to sustain efficacious psychological interventions, is a crucial research concern.

Indeed, commonalities in psychological processes underlying human suffering and psychopathology have been increasingly considered, at both conceptual and therapeutic levels (e.g., [18, 19]), as alternatives to considering the distinct mechanisms associated with specific disorders. This shift in perspective has been driven by multiple factors, including empirical evidence from epidemiological studies pointing to high comorbidity rates among mental health diagnoses both in adult [10] and adolescent [8, 20] samples. Additionally, the tendency of mental health problems, including ADs, to predict and cascade both within and between disorders throughout individuals' lives has been consistently reported in the literature (e.g., [14, 21]). While disorder-specific interventions (i.e., interventions focused on a single diagnosis) seem to yield some unintended improvements in non-targeted comorbid disorders [22, 23], they may not comprehensively address the complex interplay and dynamics observed among mental health disorders. This overlap and continuity among and within classes of disorders indicate the presence of common underlying mechanisms, thereby suggesting that treatments should be conceived to address broader processes rather than focusing solely on the specificities of certain disorders.

Transdiagnostic approaches aim to identify common elements that cut across mental health disorders, thus better reflecting the complexity and dimensionality of the human experience, and more accurately representing the reality of mental health problems. These approaches may offer several advantages. For example, transdiagnostic interventions may be more efficacious in the treatment of comorbid disorders and in preventing future mental health conditions (e.g., [24, 25]). As such, a growing body of empirical research points to the efficacy of transdiagnostic interventions in multiple disorders (e.g. [25–30]) as well as their equivalence to diagnosis-specific interventions [31]. Moreover, transdiagnostic approaches do not rely on specific diagnosis categories outlined in the Diagnostic and Statistical Manual of Mental Disorders (5th ed., DSM-5; [32]), thus allowing to target symptoms associated with subclinical conditions. Transdiagnostic approaches may also have practical and economic benefits, including shorter treatment lengths and reduced need for future access to mental health services (e.g., [25, 33]). Furthermore, it may be easier to train clinicians in transdiagnostic approaches since a single protocol can be applied to multiple disorders, instead of requiring a separate protocol for each disorder [33].

Acceptance and Commitment Therapy (ACT) is a widely researched and empirically sustained transdiagnostic approach to behavior change (e.g., [18, 34–36]) addressing both psychopathology (suffering) and psychological health. Within this framework ([37]), psychological suffering (and mental health disorders) arises from the interdependent interactions between six core processes (Cognitive Fusion, Experiential Avoidance, Attachment to the Conceptualized Self, Dominance of a Conceptualized Past/Feared Future, Lack of Values Clarity, and Inaction, Impulsivity or Avoidant Persistence,see supplementary material for a detailed description of each process). Together, these processes sustain Psychological Inflexibility (PI), a rigid pattern in which internal experiences (e.g., thoughts, emotions) dominate over contextual cues, undermining the individuals’ ability to persist in and/or change behavior to pursue chosen values ([38]). Problematic behaviors associated with mental health problems may stem from the engagement in psychologically inflexible strategies (e.g., perceiving thoughts as literal representations of reality – i.e., cognitive fusion -, and/or avoiding specific relevant situations to minimize unwanted internal experiences—inaction, impulsivity or avoidant persistence driven by experiential avoidance) that reinforce one another, becoming more rigid and entrenched over-time, and ultimately narrowing the individuals’ lives. ACT aims to reverse PI processes through the cultivation of Psychological Flexibility (PF), which refers to the ability to be in contact with the present moment, regardless of unpleasant internal experiences, while adapting and persisting in behaviors aligned with valued life directions [39]. PF entails six interrelated processes, each representing the opposite of one of the PI processes: Cognitive Defusion, Acceptance, Self as Context, Contact with the Present Moment, Values, and Committed Action [38], see supplementary material for a detailed description of each process). Through the cultivation of PF, ACT does not aim to change the form or frequency of internal events. Rather, ACT intends to promote psychological health by changing how one relates to those events and reduce their behavioral impact, thus laying the foundation for actions that move individuals towards valued and meaningful living [38]. ACT’s perspective on psychological health is closely tied to the process of individual and idiosyncratic growth, which is defined by the gradually increasing choices individuals make to embrace the present and move towards a life worth living [39]. This perspective can be captured by the concept of flourishing, defined as a state of vitality associated with the ability to engage in functional behaviors, in meaningful relationships and to cope with the demands and stresses of life [40]. Flourishing may thus be a relevant construct indicative of desired behavior change towards valued life directions.

The parallel conceptualization of processes sustaining psychopathology (i.e., PI) and, alternatively, mental health and flourishing (i.e., PF) specified by the ACT model offers a functional dimensional approach to mental health problems. Moreover, it provides a model of treatment that enables the identification of different treatment components and of psychological mechanisms that may facilitate change [39]. Multiple meta-analyses with adult populations showed that ACT and ACT-based treatments were as effective as well-established evidence-based interventions (e.g., Cognitive Behavioral Therapy; CBT), and superior to placebo or waiting list control conditions and treatment as usual in treating depression, anxiety disorders, substance use disorders, somatic health problems and other forms of adult psychopathology (e.g., [35, 41, 42]). Regarding the mechanisms underlying change during ACT, a systematic review conducted by Stockton et al. [43] identified a lack of studies on this matter. The authors pointed that few studies examined the role of specific PF processes (e.g., committed action, values, and self-as-context) as potential mediators of change in ACT. Despite the limited research available, findings from this review suggested that PF, acceptance, and cognitive defusion mediated change in mental health outcomes while non-ACT specific processes (e.g., challenging dysfunctional cognitions) did not. Levin et al. [44] conducted a meta-analysis focused on laboratory-based component studies providing evidence for PF components impact on psychological outcomes. Specifically, significant positive effect sizes were observed for conditions promoting acceptance, defusion, present moment awareness, and values, compared to inactive conditions. Further sustaining the PI/PF model assumptions (i.e., the aim is not to directly change the form or frequency of internal events [45, 46]), larger effect sizes were observed for primary targeted outcomes (e.g., willingness to reengage in a difficult task) than for overall non-specific outcomes (e.g., intensity/frequency of negative thoughts and feelings). Network analysis studies also highlighted the theoretically proposed interconnectedness between PI/PF processes [47], and their association with mental health outcomes such as well-being/quality of life, internalizing symptoms [48, 49] and PTSD symptoms [50]. However, findings were inconsistent regarding the centrality of each PI/PF process in the network (e.g., [47, 49]). Considering the cumulative evidence, the ACT model seems to offer a suitable framework to conceptualize and intervene in adults’ suffering and mental health conditions.

Nevertheless, the role of PI/PF in adolescents’ mental health remains poorly understood, and little is known about the efficacy of ACT in this age group. Previous studies support the role of PI processes in adolescents’ suffering and psychopathology (e.g., [49–54]), as well as the role of PF in adolescents’ well-being [55, 56] and meaning in life [57]. These studies relied mostly on the Avoidance and Fusion Questionnaire—Youth Version (AFQ-Y), which is a widely used measure to assess PI and explore its relationship with psychopathology related variables (e.g., [58]). However, the AFQ-Y assesses PI uniquely in relation to cognitive fusion and experiential avoidance [59], and so the literature has been amiss in considering all six core processes of PF/PI. Failing to consider all these processes may result in a less specific and idiosyncratic perspective on the theoretical and applied suitability of PI/PF to adolescents' mental health.

At the therapeutic level, a meta-analysis by Fang & Ding [34] examined 14 studies with children and adolescents, and found support for the efficacy of ACT in multiple mental health problems. ACT outperformed waiting list control conditions and treatment as usual, and did not significantly differ from evidence based interventions (i.e., CBT) in improving negative outcomes such as anxiety and depression. Promising results have been found regarding ACT efficacy on adolescents mental health problems such as ADs [60], depressive symptoms [45, 46, 61, 62], obsessive–compulsive disorder [27–30, 63], social and school adaptation [64].

Despite the potential of ACT for promoting adolescents’ mental health, further research is needed to confidently establish its efficacy. Specifically, there is a scarcity of methodologically robust designs, including Randomized Controlled Trials (RCTs), investigating ACT interventions in this population (see [27–30, 65] for a review). Also, adolescence is a period marked by significant and rapid physical, psychological, and social changes [66], which underscores the importance of studies considering extended post-intervention follow-up periods to fully assess the utility of ACT for this age group. Moreover, because ACT's efficacy on different non-comorbid adolescent mental health problems is not clearly established, there is a gap in our understanding of ACT's transdiagnostic intervention principles (i.e., that targeting the same processes is helpful for different mental health difficulties). This gap hinders our ability to further address other complex issues in adolescent mental health, such as comorbidity and the cascading effects of mental health problems.

In light of this, it is important to understand how conceptualizations can better inform interventions to increase the well-being of adolescents with diverse ADs. Particularly, SAD and GAD are ADs that hold significant prevalence rates in adolescence: 12-month prevalence estimates of 4.8% [20] and point prevalence estimates of 9.4% [67] have been reported for SAD,12-month prevalence estimates of 2.1% [20] and 6-month prevalence estimates of 9.7% [3] have been reported for GAD. Both these disorders tend to reveal a chronic course that may fluctuate by evolving into other ADs or mood disorders in adulthood [21, 68, 69]. However, transdiagnostic approaches to these disorders in adolescence, particularly GAD, are still poorly investigated at both conceptual and therapeutic levels. ACT has been proven effective for SAD and GAD treatment in adults [68–73]. To our knowledge, only few studies pointed to ACT efficacy for SAD [60, 74, 75], and only one considered a sample that included adolescents with GAD [60]. Thus, research on the efficacy of ACT on adolescent SAD and GAD is still largely missing, and mechanisms underlying change have not yet been investigated.

### AIMS

Given the scarcity of research on the applicability of ACT’s conceptual premises to adolescents, the first aim of this study is to empirically test PI/PF as accurate conceptualizations of suffering and flourishing in adolescents. As stated in the report by the Association for Contextual Behavioral Science (ACBS) Task Force [76], understanding the relationships between processes as well as their specific associations with relevant outcomes may better guide the development and delivery of interventions based on PI/PF processes. To do so, we will:Explore PI/PF processes networks and their association with adolescents’ anxiety symptoms and flourishing in a community sample (Study I) to provide for an initial understanding of the structural relationships between PI/PF processes in adolescents and their experience of anxiety and flourishing. We expect PI/PF processes to present interconnected relationships between each other. Moreover, we expect all PF processes to positively associate with flourishing and negatively associate with anxiety, even when considering all processes simultaneously. Contrarily, all PI processes are expected to associate negatively with flourishing and positively with anxiety, also when considering all processes simultaneously. These expected results align with ACT’s conceptual model as well as with preliminary evidence found in adults (e.g., [47, 48]). Given the exploratory nature of this study, and the inconsistent and limited findings on the centrality of each PI/PF process (e.g., [47, 49]), no hypothesis were raised regarding the strongest and most influential ACT processes in the networksInvestigate pathways linking PI/PF processes with flourishing and anxiety symptoms, and that models’ invariance across adolescents samples (clinical SAD, clinical GAD and mentally healthy groups; Study II). Given previous research on the associations between PI/PF and positive (e.g., well-being; e.g., [55, 57]) and negative (e.g., emotional dysregulation [52, 54],) mental health outcomes in clinical (e.g., social anxiety disorder [53],) and non-clinical samples (e.g., [51]) of adolescents, we expect similar pathways liking our variables across all groups (path invariance) and different mean levels between the clinical and the mentally healthy groups (partial mean invariance). Specifically, we expect clinical groups to present higher levels of PI and lower levels of PF compared to the healthy adolescents group.

As a second aim of the current work, we intend to contribute to filling the gap on the efficacy of ACT as a transdiagnostic approach to adolescents' SAD and GAD and amplify the transdiagnostic application of ACT to adolescents presenting these disorders (Study III). To do so, we will adapt, implement, and investigate the efficacy of an ACT Intervention to adolescents presenting SAD or GAD by exploring:Changes in primary (i.e., anxiety symptoms) and secondary (i.e., flourishing and PI/PF processes) outcomes following intervention. In view of the scarce but promising research on ACT efficacy in adolescents’ SAD [60, 74, 75], and GAD [60], improvements are expected at post-intervention for the two intervention groups (i.e., SAD and GAD), in comparison with a control group.The stability of change over time (i.e., 3 and 6 months after intervention completion). We expect improvements in the two intervention groups to be maintained.The equivalence of the efficacy of the same intervention delivered to the two intervention groups (i.e., SAD and GAD). Even though this aim has not yet been addressed, considering ACT conceptual and therapeutic transdiagnostic premises, similar effects on outcome measures are expected for both clinical groups.Mechanisms of change following the intervention in both intervention groups. Based on research conducted with adults on PI/PF processes as mechanisms of change following ACT [43], we expect similar effects in both intervention groups, with changes in PI/PF predicting changes in primary (i.e., anxiety symptoms) and secondary (i.e., flourishing) outcome variables. Specifically, we expect increases in PF processes and decreases in PI processes to promote lesser anxiety and greater flourishing. Given the lack of research on the role of each PI/PF process in producing changes in anxiety for adolescents’ GAD and SAD and the ACT assumptions that all processes are intertwined in their contribution to human suffering / flourishing [38], there were no grounds to define specific hypothesis regarding the differential role of each PI/PF process in contributing to decreases in anxiety and increases in flourishing between the two samples of adolescents, and so no specific and process-based hypotheses are put forward.

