### Intervention and treatment integrity, feasibility and satisfaction

The same manualized ACT intervention will be delivered to both intervention groups, consisting of 13 individual weekly sessions delivered online through videoconference; this is mandatory for investigating if the same intervention similarly impacts outcomes in participants presenting with diverse diagnostics. The intervention will be developed based on the PF model of ACT [37] and the choice-point model [82], and it will result from the adaptation of the *ACT@TeenSAD* intervention for adolescents with SAD (a 10-session manualized ACT intervention delivered online; Vagos et al., 2021), as well as the integration/modification of sessions’ exercises based on extensive research on ACT, ACT for ADs, and ACT for adolescents, and on the research team’s clinical expertise with adolescents and in delivering ACT based interventions. The ACT intervention for adolescents with ADs will include sessions addressing the functioning of the human mind (e.g., the survival machine, the problem-finding and problem-solving machine), creative hopelessness, the six core processes of PI/PF (e.g., acceptance of difficult thoughts, emotions, and sensations, values clarification), and revision of gains and relapse prevention (cf. Table 1). Each session will have an approximate duration of 1 hour and will be composed of experiential exercises, metaphors, images, and mindfulness practices targeting the specific topic of the session. Participants will be invited to complete between-session tasks as often as they can, in order to practice the strategies addressed in each session (e.g., present moment awareness practices) in real-life contexts. Several aspects will be taken into consideration by the research team members when developing and implementing the intervention to ensure treatment integrity. For example, the research team will seek training in ACT-based approaches, ongoing supervision by experienced psychologists, inclusion of clear and informative descriptions of exercises, as well as therapist lines (e.g., examples of questions to guide adolescents) in the intervention manual, and therapist’s report on treatment adherence after each session.

**Table 1 Tab1:** Intervention Outline

Session	Contents

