### Data analysis

IBM SPSS Statistics 25 will be used to conduct descriptive analysis. In study I, network analysis will be performed and visualized using R (Version 4.1.3). Network nodes will represent the scores for each PI/PF subscales and total scores for anxiety and flourishing measures. Edges will represent the weight of the correlations between the individual nodes. Centrality metrics (e.g., degree of centrality) will also be computed to investigate how important and influential each node is in the network. In study II, Mplus will be used to investigate the adjustment of a path analysis linking PI/PF processes to anxiety and flourishing, based on overall, comparative and residual based fit-indices. The moderator effect of groups (clinical SAD, clinical GAD and healthy adolescents) in those pathways will be estimated, testing for equality of pathways and means. In Study III, the IBM SPSS Statistics 25 will be used to explore treatment effects using Mixed ANOVAs and considering assessment moments as the within-subject and groups (SAD and GAD receiving intervention and Control Groups) as the between-subject effect; interaction effects will also be considered. Additionally, Mplus will be used to examine mechanisms of change after the intervention by performing two-wave latent change score models. These models allow to explore not only if significant changes emerged across assessment moments, but also to investigate the impact of changes in PI/PF constructs on changes in anxiety or flourishing. All Study III analyses will be carried out according to an intention-to-treat principle as suggested by the CONSORT guidelines [77]. Therefore, all participants randomized will be included in the statistical analyses and analyzed according to the group they were assigned regardless of having received/completed or not the intended intervention. Efforts will be made to obtain outcome data for all participants, even if they do not complete the intervention. If data is missing (e.g., participant refused to provide data, participant was unreachable, etc.) the last observation carried forward method will be employed.

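### Study III's stated model leaves out therapist: ACT-versus-control errors may be understated, and the SAD-GAD contrast is exposed if therapists' caseloads are uneven

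*Protocol article*

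**What the plan says.** The second aim (Protocol article, AIMS) contains two comparisons that matter here. The first is efficacy: "improvements are expected at post-intervention for the two intervention groups (i.e., SAD and GAD), in comparison with a control group". The second is "The equivalence of the efficacy of the same intervention delivered to the two intervention groups (i.e., SAD and GAD").

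Under Intervention and treatment integrity, the treatment is described as "consisting of 13 individual weekly sessions delivered online through videoconference". Integrity measures include a "therapist’s report on treatment adherence after each session". That section has research team members implementing the intervention, but it does not say how many therapists there are or how cases are shared among them. The Discussion, in its paragraph on foreseen limitations, says that the control group receives no intervention within the project.

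Data analysis fixes the Study III efficacy model as "Mixed ANOVAs and considering assessment moments as the within-subject and groups (SAD and GAD receiving intervention and Control Groups) as the between-subject effect", with their interaction. Mechanisms of change are examined by "performing two-wave latent change score models". Neither model names therapist. The Sample size section uses a two-group repeated-measures calculation with no allowance for clustering.

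**The concern.** Adolescents who share a therapist may do better or worse together. Controls have no therapist, so any such clustering sits on the ACT side only and the design is partially nested. A Mixed ANOVA with group and time as its only factors counts every ACT participant as an independent observation. If therapists differ, the ACT-versus-control p-values are then too small for a claim meant to hold beyond the therapists who took part.

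The SAD-GAD comparison is exposed in a different way. Randomisation is to ACT or control within each diagnosis, so it cannot balance therapists between diagnoses. If one therapist sees mainly SAD cases and another mainly GAD cases, a difference between therapists can look like a difference between diagnoses, or can hide one. This is the trial's transdiagnostic question. The plan already protects it by excluding comorbid cases and using one manual for both groups.

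**Working it through.** **Inputs from the article.** 29 per group (25 plus 4 for dropout); f = 0.25; alpha 0.05; power 0.95; groups compared two at a time; 4 assessments in the power calculation; controls measured twice.

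**Inputs assumed, because the article does not give them.** Therapists per ACT group, J; therapist ICC of the change score, 0.01 to 0.10.

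**Step 1: the plan's own sample size.** For the group-by-time interaction, lambda = f² × N × m / (1 − rho). With N = 50, m = 4 and rho = 0.3, lambda = 0.0625 × 50 × 4 / 0.7 = 17.86 on 3 and 144 df, and power is 0.952. This matches 25 per group. At rho = 0.5, N = 36 is enough. The article does not state rho, so 25 is attainable but not uniquely implied. Every variant assumes independent adolescents.

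**Step 2: design effect in an ACT group.** DE = 1 + (29/J − 1) × ICC.
- J = 8, ICC 0.02: 1 + 2.625 × 0.02 = 1.05.
- J = 2, ICC 0.05: 1 + 13.5 × 0.05 = 1.675.
- J = 2, ICC 0.10: 1 + 13.5 × 0.10 = 2.35.

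**Step 3: ACT group versus control.** Only one side is clustered, so the true SE is about √((DE + 1)/2) times the nominal SE. For J = 2 and ICC 0.10 this is √(3.35/2) = 1.29. With two groups and two occasions, the interaction test is equivalent to a t test on change scores. That test was simulated with no therapist term and no true effect (40,000 runs per cell). The type I error at nominal 0.05 was:

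| ICC | J = 2 | J = 3 | J = 6 |
|---|---|---|---|
| 0 | 0.048 | 0.052 | 0.050 |
| 0.01 | 0.056 | 0.054 | 0.052 |
| 0.02 | 0.066 | 0.060 | 0.054 |
| 0.05 | 0.092 | 0.075 | 0.061 |
| 0.10 | 0.130 | 0.104 | 0.073 |

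**Step 4: SAD-ACT versus GAD-ACT at ICC 0.05, each therapist treating one diagnosis only.** The SE is √(2/29 × DE) in SD units; without clustering it is √(2/29) = 0.26.

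| Therapists in total | Per diagnosis | DE | SE | False differences |
|---|---|---|---|---|
| 2 | 1 | 2.40 | 0.41 | 0.209 |
| 4 | 2 | 1.675 | 0.34 | 0.134 |
| 6 | 3 | 1.43 | 0.31 | 0.103 |

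**Step 5: the same contrast with every therapist treating both diagnoses equally.** The therapist effect cancels from the difference. Across ICC 0 to 0.10 the error was 0.041 to 0.050, so there is no inflation. The test is slightly conservative because therapist variance stays in the error term.

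**The case against.** The strongest reply is that the size rests on facts not in the article. Therapist number, case assignment and whether therapist is recorded are details that a condensed article may leave to the full protocol. The article describes a manual with scripted therapist lines, training, ongoing supervision and adherence reports, all of which should lower the ICC. One therapist might treat every case. SAD-GAD would then be unaffected, and a therapist variance could not be estimated. Even with a handful of therapists, that variance is poorly estimated.

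Most of this stands, and it limits what can be claimed. A reader might infer that the ACT-versus-control errors are definitely too small. The article does not support that, because at ICC 0.01 with six therapists the error is 0.052. A reader might also infer that the SAD-GAD result will be a therapist difference. No statement in the article says that therapists are split by diagnosis, and the single shared manual is compatible with therapists treating both. Nor does the material show that the Mixed ANOVA must be replaced as the main analysis.

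The reply does not remove the point, because the efficacy model is stated with its factors and therapist is not among them. Standardising delivery reduces therapist variation but does not guarantee that it is zero. With a single therapist, ACT versus control cannot be separated from that person.

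**Conclusion.** The concern holds in conditional form. If more than one therapist delivers ACT and the ICC is above zero, the stated model understates the ACT-versus-control standard error for inference beyond these therapists. The consequence runs from negligible (type I error 0.052 at ICC 0.01 with six therapists per group) to material (0.130 at ICC 0.10 with two).

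The SAD-GAD contrast can be confounded by therapist only if caseloads are uneven. At ICC 0.05, complete separation by diagnosis gives 10-21% false differences with two to six therapists, and equal sharing gives about 5%. All these figures rest on assumed ICCs and therapist numbers, with 29 analysed per group. The change is worth making because it is cheap and because therapist and diagnosis, once fully aliased, cannot be separated by any later analysis.

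**What to change.** 1. State the number of therapists. Assign each one similar numbers of SAD and GAD ACT cases, before cases are treated.
2. Record the treating therapist for every ACT participant.
3. Enter therapist as a blocking factor in the SAD-GAD contrast.
4. For ACT versus control, keep the stated analysis and add a partially nested sensitivity analysis, with a therapist effect in the ACT arms only and small-sample degrees of freedom. If there are too few therapists to estimate it, show results over a range of assumed ICCs using the factor √((DE + 1)/2).
5. With only one or two therapists, limit the efficacy statement to the participating therapists.

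The cost is minor scheduling constraints, one recorded variable, a few degrees of freedom for the block, and somewhat wider intervals in the sensitivity analysis. No extra staff or participants are needed.
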